### Study setting

This study takes place in the Northeast region of the United States, in Newark, DE, and Philadelphia, PA.

### Study population

Participant eligibility for this study includes: (a) parents must identify as non-Hispanic African American cancer patients diagnosed for the first time with stage I, II, or III solid tumor cancer within the past 12 months and report being a parent or primary caregiver for at least one adolescent aged 12–18 years living at home who has been informed of the diagnosis; (b) the primary parent or caregiver is an adult living with and having responsibility for the adolescent child(ren); and (c) the diagnosed parent is defined as an adult who is a biological parent, stepparent, grandparent, or fictive kin.

Parent exclusion criteria include: (a) if the parent has a serious mental health illness (e.g., clinical depression as evidenced by the Center for Epidemiological Studies Depression Scale > 27); (b) has psychotic features or severe cognitive impairment; and (c) is not fluent in spoken English. Adolescent exclusion criteria include: (a) the adolescent is severely depressed (CDI > 25; recommended clinical cutoff) or anxious (RCMAS> 42; recommended clinical cutoff) at baseline; (b) evidence of psychotic features; (c) presence of cognitive impairment (e.g., mental retardation, severe developmental disorders) as evidenced by educational records, parental report and/or clinical impression; and (d) currently in active outpatient mental health treatment.

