#### Depression

The most widely used self-report measure is the *Children’s Depression Inventory (CDI-2)*, which was adapted from the Beck Depression Inventory (BDI) and is reliable and valid for children 7 to 18 years of age [34]. The CDI-2 includes 28 items that assess behaviors associated with depression (e.g., sleep disturbance, anhedonia, suicidality, and appetite loss). Items are rated on a 3-point scale. Raw scores are converted to T scores. T-scores of 70 and higher on the total 28-item CDI-2 scale indicate severe symptoms of depression and is an exclusion criterion. For this study, a cutoff score of 70+ or higher on the T-score will be used to screen out AA adolescents because it indicates severe levels of depressive symptoms [35, 36].

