#### Anxiety

The *Revised Children’s Manifest Anxiety Scale (RCMAS-2)* includes 49 items, rated as true or not [37]. The *RCMAS-2 yields scores for six scales*: 1) *Inconsistent Response* (INC; 9 pairs) index—new; 2) *Defensiveness* (DEF; 9 pairs)—renamed; was Lie. 4 Anxiety scales: 3) *Total Anxiety* (TOT; 40 items); 4) *Physiological Anxiety* (PHY; 12 items); 5) *Worry* (WOR; 16 items)—renamed—was Worry/oversensitivity; and 6) *Social Anxiety* (SOC; 12 items)—renamed—was Social Concerns/Concentration. Extensive reliability (α = .85 and adequate internal consistency), validity (e.g., correlation of .85 with State-Trait Anxiety Inventory [STAI] for Children and significant correlation with teacher observations), and normative data have been documented. A cutoff score of 71 (T-score) or higher will be used to screen out AA adolescents with severe anxiety [37].

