#### Depression

The *Center for Epidemiological Studies Depression Scale (CES-D)* is a widely used, 20-item self-report scale that measures the current level of depressive symptoms in the general population, with an emphasis on depressed mood during the past week [40]. Scores range from 0 to 60, with higher scores indicating more symptoms of depression. CES-D scores of 16 to 26 are considered indicative of mild depression, and scores of 27 or more indicate major depression among medical patients.

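### The adolescent anxiety exclusion is stated in two incompatible ways, and the depression exclusion carries two cut-offs whose equivalence cannot be checked

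*Protocol article*

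**What the plan says.** The adolescent exclusions under Study population apply when "the adolescent is severely depressed (CDI > 25; recommended clinical cutoff) or anxious (RCMAS> 42; recommended clinical cutoff) at baseline". Neither figure carries a score type, and neither instrument is named with its edition.

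The adolescent measures entries restate the same screen differently.

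- **Anxiety.** "A cutoff score of 71 (T-score) or higher will be used to screen out AA adolescents with severe anxiety". The same entry says that the RCMAS-2 "includes 49 items, rated as true or not". It gives Total Anxiety 40 items, with subscales of 12 (physiological), 16 (worry) and 12 (social).
- **Depression.** "T-scores of 70 and higher on the total 28-item CDI-2 scale indicate severe symptoms of depression and is an exclusion criterion". The rule is then repeated: "a cutoff score of 70+ or higher on the T-score will be used to screen out AA adolescents". On scoring, the entry says: "Items are rated on a 3-point scale. Raw scores are converted to T scores".

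Table 1 lists only the CDI-2 and the RCMAS-2 as adolescent psychological outcomes. No section converts raw scores to T-scores for either instrument, and none says which statement of the exclusion governs.

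For parents, Study population uses a CES-D score above 27 as its example of serious mental illness. The adult Depression entry says that "scores of 27 or more indicate major depression among medical patients".

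**The concern.** Both places define one baseline screen, yet they give different numbers for both adolescent instruments. For anxiety, the eligibility figure is larger than the number of items on the anxiety total, so it looks unusable as a raw score. As a T-score it is far from the figure in the measures entry.

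Three things depend on this. The cut-offs fix the population to which the result applies, and one of them truncates the baseline of the CDI, the primary outcome measure. They also decide which families are referred elsewhere instead of enrolled (Recruitment of participants), so an anxiety threshold that nobody can reach would disable that part of the screen. Finally, a reader of the trial report could not tell which adolescents had been kept out.

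**Working it through.** The article states no derived figure here beyond the item counts, so the check is one of score ranges.

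**1. Item counts (adolescent Anxiety entry).** Total Anxiety = 12 + 16 + 12 = 40, which reproduces the stated 40. The remaining items are 49 − 40 = 9, which matches the 9 given for Defensiveness.

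**2. RCMAS > 42, read in each possible way.** One point per endorsed item is assumed, since the items are true/not.

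| Reading of 42 | Range | Consequence |
|---|---|---|
| Raw Total Anxiety | 0 to 40 | 42 exceeds the maximum by 2; nobody is excluded for anxiety |
| T-score | 42 is attainable | Contradicts the T-score rule of 71 or higher |
| Count over all 49 items | 0 to 49 | 42 is attainable, but the count mixes in the 9 Defensiveness items, and the article describes no such anxiety score |

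On the T-score reading with whole-number scores, one rule excludes from 43 upward and the other from 71 upward. An adolescent scoring 43 to 70 (70 − 43 + 1 = 28 score values) is excluded by one and admitted by the other.

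**3. CDI > 25, read in each possible way.** The CDI-2 has 28 items on a 3-point scale. The article does not give the item coding, so both obvious codings are shown.

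| Reading of 25 | Range | Consequence |
|---|---|---|
| Raw, items scored 0–2 | 0 to 28 × 2 = 56 | 25 lies inside the range; it may or may not correspond to T = 70 |
| Raw, items scored 1–3 | 28 to 28 × 3 = 84 | The minimum already exceeds 25; everyone would be excluded |
| T-score | 25 against 70 | Contradicts the measures entry; whole scores 26 to 69 are treated differently |

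The first reading is the natural one, and under it no contradiction can be shown. What is certain is that one exclusion carries two numbers, that one of them has no score type, and that the article has no conversion to link them.

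**4. CES-D.** Above 27 and 27 or more differ only at a score of exactly 27.

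**The case against.** The best defence is that the measures entries already supply workable rules. Each names the edition in Table 1, gives the metric and the direction, and says that it will be used for screening. Staff following those entries would screen consistently. This lowers the practical risk but does not remove the conflict, because the formal eligibility list is the other statement and nothing gives the measures entries precedence.

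A second defence concerns the CDI. Since the article says that raw scores are converted, 25 may simply be the raw counterpart of T = 70. This stands. A reader might infer that the primary outcome measure is screened by two contradictory rules, but the article supports only an unlabelled metric.

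Other stronger readings go further than the article allows.

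- **Percentages excluded.** With T-scores assumed normal with mean 50 and SD 10, about 79% of a reference population would exceed 42 and about 2% would exceed 71. The article states neither that metric nor that distribution. Its Background reports clinical distress in 22–33% of children of parents with cancer, so a normative reference would not describe this sample in any case.
- **Sites enrolling different populations.** The centres are described as places of recruitment, and the assessment team arranges the face-to-face evaluation. Nothing shows the centres screening separately.
- **A CES-D contradiction.** The parent figure is an exclusion example, while the measures entry describes a severity band. A protocol may set the two apart, so this is a wording point.
- **Bias in the treatment comparison.** Screening and baseline assessment come before allocation and are the same for both arms. The stated sample-size inputs (d = 0.38, correlation 0.68, 70% retention) include neither cut-off.

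**Conclusion.** The anxiety exclusion is wrong as written. On the instrument described, RCMAS > 42 is unattainable as a raw Total Anxiety score (maximum 40). As a T-score it is incompatible with 71, with 28 whole-number values falling between the two rules. The only count that could exceed 42 uses all 49 items, which the article does not present as an anxiety score. The raw-score conclusion rests on the article's item counts and on one point per endorsed item; the T-score conclusion needs no outside norm.

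The depression exclusion is ambiguous but not shown to be contradictory. The CES-D boundary is a minor wording point.

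The effect is on who is enrolled, who is referred out and how far the result generalises. How many adolescents are affected cannot be calculated from the article. The internal validity of the randomized comparison is not in question.

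**What to change.** Reconcile Study population with the adolescent Depression and Anxiety entries. Each instrument should have one cut-off, stated on a named edition, a named scale and a named score type (raw or T), with the same number and the same inequality in both places. If the CDI figure of 25 is meant as a raw equivalent of the T-score rule, say so and give the conversion used. Check the screening logs to establish which rule was applied to each family already screened, and report that rule. In the same edit, align the CES-D wording at a score of exactly 27, or state that the exclusion and the descriptive band differ on purpose.

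The choice of cut-off belongs to the investigators. The cost is a short protocol clarification and a log review, with no change to the design, sample size or analysis.

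### The adolescent exclusion cut-offs are stated twice without reconciliation, and RCMAS > 42 agrees with the RCMAS-2 T-score rule on no anxiety scale the article describes

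*Protocol article*

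**What the plan says.** The protocol article gives the adolescent depression and anxiety exclusions in two places.

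- **Study population.** An adolescent is excluded if "the adolescent is severely depressed (CDI > 25; recommended clinical cutoff) or anxious (RCMAS> 42; recommended clinical cutoff) at baseline". No edition, subscale or score type is named.
- **Depression (adolescent outcomes).** On the CDI-2, "T-scores of 70 and higher on the total 28-item CDI-2 scale indicate severe symptoms of depression and is an exclusion criterion", and for this study "a cutoff score of 70+ or higher on the T-score will be used to screen out AA adolescents". On scoring: "Items are rated on a 3-point scale. Raw scores are converted to T scores".
- **Anxiety (adolescent outcomes).** The RCMAS-2 "includes 49 items, rated as true or not". Total Anxiety is listed with 40 items, made up of Physiological Anxiety (12), Worry (16) and Social Anxiety (12). Then: "A cutoff score of 71 (T-score) or higher will be used to screen out AA adolescents with severe anxiety".

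Table 1 lists the CDI-2 and RCMAS-2 as the instruments given at baseline. No section converts one set of cut-offs into the other or says which one governs.

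**The concern.** Both sets are worded as operative eligibility rules, with different numbers, and only one set carries a score type. Under Recruitment of participants, families are screened on these measures at intake and ineligible families are referred elsewhere. The figures therefore decide who is enrolled and who is referred out.

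The CDI is also the primary outcome, and its baseline value is the ANCOVA covariate in the analysis of Primary aim 1. The CDI entry threshold sets the upper end of the baseline distribution, and so could affect the pre-post correlation of 0.68 used under Statistical power. Eligibility violations cannot be counted consistently while two unreconciled rules stand.

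**Working it through.** **Inputs from the article.** RCMAS-2: 49 true/not items; subscales of 12, 16 and 12; Total Anxiety 40 items; T-score cut-off 71 or higher. CDI-2: 28 items on a 3-point scale; T-score cut-off 70 or higher. Study population: RCMAS > 42, CDI > 25.

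**Assumptions not in the article.** One point per RCMAS-2 item; CDI-2 items scored 0 to 2; T-scores normal with SD 10 and mean 50, the mean varied from 45 to 60.

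**Step 1: reproduce the Total Anxiety length.** 12 + 16 + 12 = 40, which matches the stated figure.

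**Step 2: RCMAS > 42 as a raw score.** The maximum raw Total Anxiety score is 40 × 1 = 40. Exceeding 42 needs at least 43, so the rule cannot be met and excludes 0%. The subscales, with maxima of 12, 16 and 12, cannot reach it either. A count over all 49 items could exceed 42, but it would add 49 − 40 = 9 items from outside Total Anxiety, and the article lists no 49-item anxiety scale.

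**Step 3: both figures as T-scores.** With m the assumed mean, the proportion excluded is P(T > c) = 1 − Φ((c − m)/10). At m = 50:

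- RCMAS > 42: 1 − Φ(−0.8) = 0.788
- RCMAS-2 T ≥ 71: 1 − Φ(2.1) = 0.018
- CDI > 25: 1 − Φ(−2.5) = 0.994
- CDI-2 T ≥ 70: 1 − Φ(2.0) = 0.023

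| Assumed mean | RCMAS T > 42 | RCMAS T ≥ 71 | CDI T > 25 | CDI T ≥ 70 |
|---|---|---|---|---|
| 45 | 61.8% | 0.5% | 97.7% | 0.6% |
| 50 | 78.8% | 1.8% | 99.4% | 2.3% |
| 55 | 90.3% | 5.5% | 99.9% | 6.7% |
| 60 | 96.4% | 13.6% | > 99.9% | 15.9% |

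Treating T-scores as whole numbers changes little: at mean 50, 77.3% for > 42 and 2.0% for 71 or higher. The two anxiety rules disagree whatever the distribution, because any T-score from 43 to 70 is excluded by one and admitted by the other.

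**Step 4: CDI > 25 as a raw score.** The maximum is 28 × 2 = 56, so > 25 can be reached. The article says raw scores are converted to T-scores but gives no conversion. Whether a raw score above 25 corresponds to T of 70 or higher can be neither confirmed nor refuted.

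**The case against.** One could reply that the measure descriptions are the operational text. The CDI-2 paragraph states version, total scale, score type and threshold, and the RCMAS-2 paragraph states version, score type and threshold. The unlabelled figures would then be shorthand, perhaps raw equivalents, in an article that condenses a fuller protocol and does not show the screening form. Screening also precedes randomization and applies equally to both arms, so the treatment comparison is not biased.

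Much of this stands. The discrepancy affects who is enrolled and how eligibility is reported, not the internal validity of the comparison. The raw-equivalent explanation remains open for the CDI, and reading CDI > 25 as a T-score sits badly with its description as marking severe depression. The same explanation fails for the RCMAS: 42 lies above the maximum of every anxiety scale listed, so it cannot be the raw equivalent of T of 71 or higher on any of them. Condensing an article explains missing detail, but not two different stated thresholds.

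A reader might also infer that the anxiety criterion as written screens out nobody. That holds only on the raw reading. The Study population section names no score type, and the only RCMAS-2 screening metric the article names is the T-score, under which > 42 does the opposite and excludes most adolescents. Nor does the article show that the two centers would screen differently. It refers to a single assessment team and describes no site-specific screening.

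**Conclusion.** The point holds in this form: the adolescent cut-offs are stated twice without reconciliation, and the anxiety pair conflicts on every anxiety scale described. RCMAS > 42 is unreachable as a raw score, given one point per item. As a T-score it would exclude about 79% (62–96%), against about 2% (0.5–14%) for 71 or higher. That the two T-score rules differ is certain; the percentages are illustrative and rest on the assumed normal distribution.

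For the CDI the conclusion is weaker. There is a conflict if 25 is a T-score. If it is a raw score, the documents do not allow equivalence to be judged, so a claim that the two CDI rules are incompatible would go too far. What is established for the CDI is a second threshold with no score type and no link to the first.

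This is an internal inconsistency in an enrolment threshold, and should be corrected before the rule is relied on for screening or for counting eligibility violations.

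**What to change.** Reconcile Study population with the adolescent Depression and Anxiety measure descriptions. State each exclusion once, giving the instrument version (CDI-2, RCMAS-2), the scale, the score type (raw or T) and one threshold, and repeat that wording wherever the rule appears, including the screening form. Remove any figure that cannot occur on the instrument used. If a raw cut-off is kept beside a T-score, give the conversion that links them. The choice of threshold belongs to the clinical lead. Then re-check the stored baseline scores of everyone already screened against the reconciled rule, and report any who were enrolled or referred out contrary to it.

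The cost is a wording correction and a re-check of scores already held. No new data are needed.

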### Recruitment of participants

The target sample will be primarily recruited from the Helen Graham Cancer Center and community recruitment sites, with Kimmel Cancer Center of Jefferson University serving as a secondary recruitment site. Eligible AA patients will first be sent a letter, and then called up to twice to see if they are interested in the prevention program. If a patient expresses an interest in the study, he or she will first sign a release of information, so the recruiter can contact him or her. The recruiter will then mail out a recruitment letter and brochure and will then contact the patient by telephone to explain the study. If the patient continues to meet study inclusion criteria and his/her adolescent child wants to participate, the assessment team will schedule a face-to-face evaluation with parents and adolescents either at the oncology clinic, the patient’s home, or at the University of Delaware, depending on what the patient/family prefers.

Following informed consent during the intake meeting, the patient and adolescent will be fully screened for study inclusion criteria (e.g., screened for parental and adolescent depression/anxiety). If patients, family members, and adolescents are appropriate for the study, the recruiter will fully explain the study and participants will sign consent/assent forms. Families that are deemed ineligible during screening will be provided with an appropriate referral for additional services (at cost to them when applicable). Parents and adolescents will then separately fill out baseline assessments using a HIPAA-secured tablet. This process should take no longer than 60 min to complete.

### Randomization

Randomized permuted blocks will be used to allocate groups of parent-adolescent dyads to each study arm (FFCT or PED). The data manager will prepare complete sets of allocations which will be placed in sequentially numbered sealed opaque envelopes containing treatment assignments for each group of 5 to 8 families. Once 5 families are recruited, group allocation will be made after a week has elapsed without any additional family participants recruited or once 8 families have been recruited, whichever occurs first.

The assessment team will be blind to the allocation condition and know only the serial numbers. At randomization, following baseline assessments, only the program manager opens the envelope for the group’s allocation. This approach provides both dynamic balancing and prospective partial blinding of the project manager to treatment assignment. At the end of the study, unused sealed envelopes will be retained along with the log to assure that randomization has been carried out as assigned.

### Attrition

We will implement a variety of procedures to reduce attrition. At the baseline assessment, all families are informed of and agree to the follow-up assessments before they are randomized. As part of the intake assessments, all patients complete a form listing their home address, phone numbers, and at least 3 contact persons who will always know the family’s location. The locator information is updated at each data collection point and is an important tool for finding patients who move during the follow-up phase.

Families are scheduled for the next follow-up at the previous appointment and are reminded of their appointments by a series of phone calls and mailings. A letter thanking families for participating in the study is sent within 1 week of randomization, and reminder letters are sent 1 week before the assessment is scheduled. Confirmation telephone calls are made 24 h prior to a scheduled follow-up appointment. When necessary, staff will travel to families’ homes, Helen F. Graham Cancer Center, or other locations to complete assessments. We will also mail cards to each caregiver and adolescent on their birthdays and all major holidays. These cards will be initiated as soon as the family agrees to participate. The cards remind participants of their involvement in the project and enable the investigators to determine if a family has moved (e.g., card is returned). These retention procedures are standard practice and usually produce research retention rates of 85% or better. In order to help verify external validity of the final sample, we will track the number of families who make it to intake, randomization, and treatment. Refusers and dropouts will be documented, and we will call these families to gather information about barriers and facilitators to treatment.

To increase retention and attendance, we will provide money for public transportation, food, drinks, and an onsite babysitter to care for any younger children when families participate in the 5-session prevention program. Removing barriers for completing assessments are important when working with a lower income urban minority population. To increase the likelihood of completion of the 4 assessments (baseline, post-treatment, 6 and 12-month follow up), we will compensate adolescents and one parent each: $30 for 1 parent and $30 for adolescents at the baseline assessment; $35 for 1 parent and $35 for adolescents at the post-treatment assessment (week 8), $40 for 1 parent and $40 for adolescents at the 6-month follow-up, $40 for 1 parent and $40 for adolescents at the 12-month follow-up assessment.

